# 1. INTRODUCTION

## 1.1. Background

Walking impairment is a relevant symptom in patients with neurological diseases. For example, in multiple sclerosis (MS), symptoms such as weakness and spasticity, loss of proprioception and coordination, vestibular, cognitive and visual dysfunction, fatigue and pain can all contribute (Pearson et al., 2004). With Parkinson's disease, mobility is determined by rigidity, hypo- and bradykinesia, flexion posture and postural instability, and other symptoms such as REM sleep disorder associated fatigue can have important effects (Cheng et al., 2012). After a stroke, walking impairment is a disabling and frequent symptom (Rose et al., 2017). Approximately 75% of stroke survivors live with some form of gait disorder (Sullivan et al., 2009). Symptoms of the hereditary ataxias are progressive coordination deficits of movement and speech, and a wide-based, uncoordinated, unsteady gait (Bird, 1993). Other clinical symptoms include spasticity, neuropathy and cognitive or behavioral deficits (Bird, 1993). In patients with spastic para-or tetraplegia, acute or chronic inflammatory demyelinating polyneuropathy and motoneuron disease, walking impairment is also a main contributor to their disability, which leads to restrictions in their everyday lives. Numerous studies have shown that walking disability contributes to depression and anxiety, heavily impacts social participation and quality of life (Ochoa-Morales et al., 2019; Pearson et al., 2004). Furthermore, relevant studies have pointed out the relationship between walking disability and employment in patients with neurological disorders (Jarvis et al., 2019; Raggi et al., 2016). People who have had a stroke or MS are unable to work or participate in social activities because of their walking difficulties and impairments in activities of daily living (Jarvis et al., 2019).

Patients post stroke are usually treated intensively in the acute and subacute phases to enhance motor performance. This is because the recovery of walking and further sensorimotor and cognitive functions mainly takes place within the first 11 weeks after a stroke. A principle here is: the milder the paralysis, the faster the recovery (Jørgensen et al., 1995). As for patients with more severe disability, *the* principle of neurorehabilitation is 'use it or lose it' [function] (Shors et al., 2012). In patients with amyotrophic lateral sclerosis (ALS), training is more intensive in the first, so called active phase after diagnosis, when the physical condition is better, in order to maintain the walking and other motor functions for as long as possible (Calabrò et al., 2019). In patients with a progressive disease such as MS, Parkinson's, ALS or hereditary ataxias, a main reason for undergoing neurorehabilitation is to preserve their ability to walk (Cheng et al., 2012; Wirz et al., 2001). Neurological deficits, such as walking impairment, poor coordination and balance loss, can be reduced by intensive and repetitive task-oriented training (Nilsson et al., 2001; Van Peppen et al., 2004).

Motor learning is present in patients with mild to severe disability, based on the process of neural plasticity, and can be boosted by a range of neurorehabilitation strategies (Maier et al., 2019). The principles underlying effective neurorehabilitation are well-known yet, and these are applied in inpatient and outpatient neurorehabilitation on a routine basis. A relevant review has identified the most salient principles of motor learning based on the evidence so far. These comprise massed practice, dosage, task-specific practice, goal-oriented practice, variable practice, increasing difficulty, explicit feedback in terms of knowledge of results and implicit feedback in terms of knowledge of performance (Maier et al., 2019).

The first principle, massed practice, has been defined as work episodes with very brief to no rest periods (Schmidt & Lee, 2011). In these episodes, repetitive training for a skill can be trained in a constant or blocked way (Mulligan et al., 1980). For the field of rehabilitation, this means prolonged and repeated use of the affected limb (Taub et al., 1999), which is clearly achieved for the lower limbs with a robotic gait trainer, and sufficient time for rest is ensured at the same time. Dosage generally operationalises the number of hours of therapy (Kwakkel, 2006; Veerbeek et al., 2014), the duration and frequency of sessions (Dobkin, 2005) or the stimulation of learning for the amount of training required (Wadden et al., 2017). The number, duration and frequency of the therapy sessions are specified by the clinical investigation plan. The third principle of motor learning is task-oriented training. Task-specific training assumes that changes in the condition of a task can cause a change in the required skills (Schmidt & Lee, 2011). Task-specific training i.e., training of a task such as walking facilitates motor learning and retention (Boyd et al., 2010). Fourth, goal-oriented practice indicates that when attention is focused on the effect of the movement rather than the movement itself, motor performance and learning is improved (Wulf & Prinz, 2001). Task-specific exercise and goal-oriented exercise are addressed by different factors in robot-assisted gait training (RAGT): through the targeted training of walking and the possibility of an additional virtual environment.

The fifth principle of motor learning is the progression in difficulty. This shows that training that is adapted to the learner's abilities leads to better learning outcomes than when the level of difficulty is fixed (Wickens et al., 2013). The difficulty of the RAGT can be continuously adapted by varying the difficulty of the training from passive to supportive to active and through other parameters for example body weight support and step length. Further two principles of motor learning are explicit and implicit feedback. Explicit feedback has been defined as verbal, terminal and reinforced feedback on goal attainment (Salmoni et al., 1984). Here, qualitative or quantitative feedback is given regarding a task outcome e.g., correctness and accuracy (Mazzoni & Krakauer, 2006; Subramanian et al., 2010). Implicit feedback is defined as feedback on movement performance in the form of verbal description, replays of recordings or demonstrations (Gentile, 1972). In RAGT, explicit feedback can be given by the supervising therapist and implicit feedback can be provided as

augmented performance feedback via a computer screen in front of the patient, based on the different measurements of parameters by the robot. For example, visual implicit feedback can be given on distance, duration, and number and length of steps.

In inpatient neurorehabilitation, the principles of motor learning are applied to facilitate the rehabilitation outcomes in patients e.g., with the help of robot-assisted therapy. A variety of studies has shown that RAGT is based on the theories and principles of motor learning (Bruni et al., 2018; Calabrò et al., 2018; Portaro et al., 2017). RAGT can be categorised into gait training using different systems, the stationary system and the overground system (Calabrò et al., 2016). Stationary devices are realised by a movable floor platform in a fixed structure and can be divided into treadmill gait trainers (such as the Lokomat® exoskeleton [Hocoma AG, Volketswil, Switzerland]) and programmable foot end effector trainers (e.g., the GE-O-System® [Reha Technology AG, Olten, Switzerland] and LEXO® [Tyromotion, Graz, Austria]) depending on the type of mobile platforms used (Bruni et al., 2018; Calabrò et al., 2016). The Reha Zentrum Münster uses a Lokomat® exoskeleton and a LEXO® foot end-effector trainer for RAGT in patients with neurological disabilities. The end effector system promotes the patient's own activity and enables active and more physiological gait training, due to adaptability of the pelvis support.

## 1.2 Rationale

To the best of our knowledge so far, no study has evaluated routinely used RAGT in different groups of patients with neurological diseases in an inpatient rehabilitation setting. No comparative study has ever investigated RAGT in patients with stroke, multiple sclerosis, Parkinson's Disease, spastic para- or tetraplegia caused by any type of spinal cord lesion, hereditary ataxia, acute or chronic inflammatory demyelinating polyneuropathy and motoneuron disease. These neurological diseases are associated with different symptom complexes, involving distinct central and peripheral nervous system sensorimotor areas and pathways, which is why patients may interact differently with a robotic gait trainer. In addition, no study has ever combined a quantitative and qualitative data collection approach using subjective and objective methods in these populations. Therefore, a multiple case-oriented research strategy is necessary to acquire knowledge about the outcomes from RAGT within the different patient (disease) groups, learn about similarities and differences between individual cases and neurological disorders within the study intervention period and about emerging patterns (Ababacar et al., 2020; Nordbeck, 2013). A synthesis across cases seems useful that extends beyond the comparison of similarities and differences to generate information on the reasons and explanations as to the findings from the RAGT intervention. Thus, a prospective comparative multiple case study is necessary for the development of theory, to inform the hypotheses of a follow-up randomised controlled trial (Goodrick, 2014).

### 1.3 Risk-benefit analysis

The performance of the RAGT intervention and walking/balance tests may trigger adverse events and side effects. These may include increased and reversible fatigue and mild muscle pain associated with the gait training and will be minimised by using predefined and individualised strategies for progression of difficulty and breaks if needed, as outlined in detail in Chapter 7.2. The risk of this is therefore classified as low. RAGT is performed as part of the clinical routine in inpatient rehabilitation settings using different devices, with the LEXO® robotic gait trainer being a CE marked medical device that has undergone a comprehensive risk assessment (please see below for details). Any contraindications for the RAGT and any additional exclusion criteria related to this clinical investigation will be complied with. In addition, continuous monitoring for adverse events will be performed using a structured adverse events log. In addition, the clinical investigation site is an inpatient rehabilitation centre with a large medical team that is available on a 0-24/7 basis. At weeks 1 and 4, a semi-structured observation of the intervention will take part as a qualitative study measure, and any inconveniences of the participants will be noted and taken care of. So far, based on a systematic search within the worldwide most important databases for medical devices, no results and no adverse events were reported for the LEXO and its operating software tyroS. Furthermore, no adverse events happened with LEXO® from its market introduction. With respect to the walking, mobility and dynamic balance assessments, some of them are also performed as part of the clinical routine at the clinical investigation site and at other Austrian rehabilitation centres, with the remaining being carefully selected, standardised, validated assessments with excellent psychometric properties in patients with neurological diseases. As for the walking tests, it is assumed that falls may occur in rare cases, but these may also occur outside of the physiotherapy and study assessment setting in the daily lives of patients with neurological disabilities. To keep the risk of falls as low as possible, the walking assessment will be performed along a wall and under the supervision of a trained physiotherapist. Physical contact should not take place in order not to impact test performance but will be used to avoid a fall.

The RAGT will be integrated into patients' inpatient rehabilitation and be planned at similar daytimes to reduce patient burden and facilitate comparability. The baseline and post-intervention examinations involve walking and balance tests and self-report questionnaires. This means that the patients may alternate between physical and mental activities, will be supported as required and as permissible with respect to the test instructions, and they may take a rest at any time. Therefore, the clinical investigation procedures are classified as low burdensome. Since the clinical investigation will be conducted in an inpatient rehabilitation environment, the participants will not be required to travel to the clinical investigation site.

With respect to the benefits from the RAGT, it is expected that the patients will improve their walking or gain walking ability (severely affected patients post stroke in the subacute phase). The results gained from this clinical investigation will help to optimise RAGT

protocols with respect to patients with different neurological diseases, which will contribute to better rehabilitation outcomes in the long-term. In summary, the expected benefits – treatment optimisation and more efficient and effective rehabilitation – outweigh the low-level risks and burden for patients, therefore the study procedures only represent a minor health risk and merely slight burden for patients, based on the current state of medical knowledge.

### **Risk Assessment**

The prevention of risks was carried out according to the criteria that are specified by the International Organization for Standardization (ISO) EN ISO 14971 risk management, as well as by the application of the medical device directive 93/42/EEC concerning medical devices. After risk mitigation strategies for the LEXO® robotic gait trainer have been employed by the manufacturer, risks were rated as “ACCEPTABLE”.

The overall medical benefit outweighs the risk of specific endangerments, the possible combinations of all known endangerments, as well as the total residual risk device status

### **Demonstration of an acceptable risk-benefit-ratio**

Demonstration that known and expected risks for the medical product were reduced to a minimum, and that these risks are acceptable when weighed against the benefits for the patient, when compared to current treatment options

- if there are risks arising of the use of the LEXO® system
- if the benefit/risk profile, undesirable side-effects (whether previously known or newly emerged) and risk mitigation measures are still
  - compatible with a high level of protection of health and safety and acceptable according to current knowledge/ the state of the art
  - correctly addressed by the manufacturer's current post-market surveillance plan
- if there are any specific clinical concerns that have newly emerged and need to be addressed

The risk management file identified risks arising from therapy using of the LEXO® robotic gait trainer. All identified risks were rated for their probability of occurrence (frequent, probable, occasional, remote, improbable) and for the severity of consequences (negligible, marginal, critical, catastrophic) before and after corrective actions.

The prevention of risks was carried out according to the criteria that are specified by the international standard EN ISO 14971 risk management, as well as by the application of the medical device directive 93/42/EEC concerning medical devices. After risk mitigation

strategies for the LEXO® robotic gait trainer have been employed by the manufacturer, risks were rated as "ACCEPTABLE".

The overall medical benefit outweighs the risk of specific endangerments, the possible combinations of all known endangerments, as well as the total residual risk.

### Claims on clinical safety

The LEXO® system

1. has been CE marked as a medical product class IIa in Europe according to directive 93/42/EWG
2. has passed the 60601-1 test, the machinery directive 2006/42/EG, and the 60601-1-2 test
3. is developed, approved, and produced according to the following standards: ISO 13485, IEC 62366, ISO 14971, ISO 10993, RoHS/Reach, and IEC 62304
4. has biocompatibility according to ISO 10993

The following is a summary of the risk analysis for the Lexo with the Intended Use and Intended Population described above (CE mark). Risks have been analysed and evaluated during Design and Development, Manufacturing and Feedback from customers.

The risks from all identified hazards were assessed.

### Evaluation of the overall residual risk:

ACCEPTABLE ☒ ALAP ☐ UNACCEPTABLE ☐

### Risk-Benefit Analysis:

|                                                                        |     |
|------------------------------------------------------------------------|-----|
| Med. Benefit outweighs risk of the individual hazard examined          | Yes |
| Med. Benefit outweighs possible combinations of all hazards considered | Yes |
| Med. Benefit outweighs total residual risk                             | Yes |

if no: risk is not acceptable - no placing on the market possible

The overall risk is classified by management as ACCEPTABLE (no risk or no risk that can be further minimized).

LEXO® has been tested and CE marked for the intended use and the intended population mentioned in the user manual.

### Claims on clinical safety: LEXO®

- *Has passed the 60601-1 test, the machinery directive 2006/42/EG and the 60601-1-2 test*
- *Is developed, approved and produced according to the following ISO standards: ISO 13485, IEC 62366; ISO 14971; ISO 10993 and IEC 62304*

An adverse event data base report has been made based on the systematic search within the worldwide most important databases for medical devices. The results cover adverse event reports, product recalls, and complaints for all years available up to present. Identified search terms targeted Tyromotion devices and software as well as equivalent devices named in the clinical evaluation report (CER). No results and no adverse events were reported for any Tyromotion device and its operating software tyroS version 6.1.

No adverse events happened with LEXO® from its market introduction.

### **Expected benefit**

The LEXO® device is intended for the robot-assisted gait rehabilitation of patients with a limited walking ability due to neurological damage to the central and peripheral nervous systems, as well as due to orthopaedic, geriatric and pediatric symptoms.

Depending on national differences, the LEXO® is typically used in a physiotherapy environment in order to support, enhance, and intensify therapy. The repetitive movements of the lower limbs, and consequently of the gait pattern, generate intrinsic and extrinsic stimuli which favour the reorganisation of the brain. Repeated, active practice and training encourages the neuronal plasticity and thus changes (adjustments) of synapses, nerve cells or even entire brain areas to recover lost movements. For more details, refer to the LEXO® user manual.

With the LEXO® it is possible to reach a high number of steps and intensity. The device is easy to handle and it takes not much time i.e., ~2 minutes to setup the patients.

*Claims on clinical performance: The LEXO® is intended for the robot-assisted gait rehabilitation of patients with a limited ability to walk. The LEXO® system has an easy and fast setup, is an end-effector, enables active walking, gamification, has a compact design.*

Main features:

- Weight support with harness system or saddle and trunk fixation
- Active 3D Pelvis
- Passive/Assistive/Active Walking
- Backrest for unstable patients
- Patient self-transfer and lifter transfer
- Variable step length, cadence, velocity (electrically adjustable)
- Augmented performance feedback

### **Results of a systematic evaluation of the specific scientific literature**

- Walking ability (independent walking), gait velocity and maximum walking distance are central parameters for measuring the success of rehabilitation of gait after a stroke.
- The use of robotics can positively affect the outcome of a gait rehabilitation in patients with stroke (Bruni et al., 2018).

- People who receive electromechanical-assisted gait training in combination with physiotherapy after stroke are more likely to achieve independent walking than people who receive gait training without these devices (Mehrholz et al., 2017).
- The earlier the training starts, the better the gait recovery (Bruni 2018). People in the first three months after stroke and those who are not able to walk seem to benefit most from robot-assisted gait training (Mehrholz et al., 2017). Robotic rehabilitation is a valuable post-stroke treatment, leading to the best results in the subacute phase (Bruni et al., 2018).
- With respect to gait velocity, gait training assisted by end-effector apparatus (like the LEXO®) lead to a statistically significant and clinically relevant improvement in post-stroke patients, while none of the other interventions (i.e. no gait training, conventional gait training (reference category), training on a treadmill with or without body weight support, training on a treadmill with or without a speed paradigm, and electromechanically assisted gait training with exoskeleton apparatus) improved gait velocity to any significant extent (Mehrholz et al., 2018).

With respect to the maximum walking distance, gait training assisted by end-effector apparatus and treadmill training with body weight support led to a significant improvement.

## **2 PURPOSE, OBJECTIVES AND HYPOTHESES OF THE CLINICAL INVESTIGATION**

### **2.1. Study purpose**

The purpose of this clinical investigation is to investigate the feasibility and acceptability and compare the preliminary effects of RAGT a mixed population with neurological diseases consisting of patients with stroke in the subacute and chronic phases and with severe and mild to moderate disability, MS, Parkinson's Disease, spastic para-or tetraplegia, mild to medium grade hereditary ataxia, acute or chronic inflammatory demyelinating polyneuropathy and motoneuron disease. A further purpose of this clinical investigation is to synthesise quantitative and qualitative results for examining causality i.e., the extent to which the RAGT intervention may have caused the outcomes.

### **2.2. Primary objectives**

The primary objective of this clinical investigation is to explore the feasibility of the methods and of a full-scale randomised controlled trial as assessed by the recruitment rate, retention rate and adherence rate, adverse events as monitored by a structured log, the acceptability of the intervention as evaluated by a Smiley Likert Scale asking four predefined questions, as well as a semi-structured observation during the RAGT intervention for understanding the intervention context and process.

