In practice, this comparative multi case study will involve the analysis and synthesis of the similarities, differences and patterns across multiple cases, with the shared common goal of gaining knowledge about the feasibility, acceptability and preliminary effects of RAGT. Case selection will be performed using two different strategies: within disease groups, the 'Most Similar Systems Design' (MSSD) will be applied and between disease groups, the 'Most Different Systems Design' (MDSD) (Anckar, 2008; Przeworski & Teune, 1970) will be used, considering the 8 neurological disease groups with different symptom complexes involving distinct central and peripheral nervous system (CNS, PNS) sensorimotor system areas and pathways (upper and lower motor neurons including both the cerebrum and spinal cord, extra pyramidal motor system, peripheral nervous system and cerebellum). As for MSSD, it will mean to purposively choose study patients that are similar in as many background characteristics as possible, but without systematically matching cases on all the relevant control variables. As for MDSD, the strategy will be to purposively select patients that are as different as possible with respect to extraneous variables. The basic logic is that differences cannot explain similarities (Przeworski & Teune, 1970). Both a quantitative and qualitative data collection and analyses will be used to achieve these goals.

All cases will receive RAGT training using a standard protocol that will allow individualisation according to the neurological disease, functional status and walking performance of the patient, the stage of the disease, age of the patient etc. No control intervention will be used because this is the first study to compare a LEXO-based RAGT in patients with 7 different neurological disorders, one of them including patients at different stages of recovery and functional status (subacute, severe stroke and chronic, mild to moderate stroke).

Figure 4 presents a sample flow diagram of the clinical investigation including analyses.

[figure not shown]

**Figure 4:** Sample flow diagram of the clinical investigation including analyses

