***additional measures for the patients.***

The criteria for feasibility success will be:

- a) a target recruitment rate 3 patients per month.,
- b) a target retention rate of 85%,
- c) a target minimum adherence rate of 75% to the RAGT interventions (12 sessions out of a maximum of 16)

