## **7.7 Medical care after exit from the clinical investigation**

In principle, the intervention of this clinical investigation is part of the clinical rehabilitation routine i.e., the usual treatment of the patients and not an add-on treatment. After patients have terminated their participation in this study, their treatment will be continued according to their treatment scheme in the same way as during the study. This includes their medication and usual physiotherapy or any other medical treatment or assessment.

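### The primary endpoint claims feasibility of a full-scale randomised trial, but a single-arm study gives no information on acceptance of randomisation or retention in a comparator arm

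*Protocol*

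**What the plan says.** Section 2.2 gives the primary objective as follows: "explore the feasibility of the methods and of a full-scale randomised controlled trial as assessed by the recruitment rate, retention rate and adherence rate". The same sentence adds adverse events, acceptability on a Smiley Likert Scale and semi-structured observation of training sessions. Section 4.8 and the synopsis define the primary endpoint in the same terms.

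Under its heading on recruitment, retention and adherence rates, section 4.8 says that predefined criteria will be used to explore feasibility both of the methods and of running a larger trial. It then lists them: "The criteria for feasibility success will be" (a) "a target recruitment rate 3 patients per month", (b) "a target retention rate of 85"%, and (c) "a target minimum adherence rate of 75% to the RAGT interventions (12 sessions out of a maximum of 16").

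On the design, section 4.1 says "All cases will receive RAGT training using a standard protocol" and "No control intervention will be used because this is the first study to compare a LEXO-based RAGT" across these disorders. Section 7.2 places the training within routine inpatient care. Section 7.7 says "the intervention of this clinical investigation is part of the clinical rehabilitation routine i.e., the usual treatment of the patients and not an add-on treatment". Table 8 (section 7.1) enters the 45-minute sessions under time within clinical routine and shows no added time for them.

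Section 8.2 on the planned analysis defines the recruitment rate as consenting patients over eligible patients, and retention as completers over the total sample. The limitations list includes the absence of a control group, and the text below it says that the results can be used to design a full-scale randomised trial.

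**The concern.** A randomised trial asks two things of patients that this study does not: to let chance decide what they receive, and to stay in follow-up if chance gives them the comparator. The protocol nevertheless attaches the label of feasibility success, for a larger trial as well as for the methods, to three figures collected entirely in patients who all receive RAGT.

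If the criteria are met, the primary endpoint as worded invites the statement that a full-scale randomised trial has been shown to be feasible. That matters here because a larger randomised trial at the same site is already foreseen in the agreement described in sections 6.1 and 6.6. Planning figures for its recruitment and drop-out could be carried over from a study that never observed either process under randomisation.

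**Working it through.** **The protocol's own figures.** The eight strata in section 5.3 sum to 5 + 5 + 5 + 5 + 2 + 2 + 2 + 2 = 28, as stated. The adherence threshold is 12/16 = 75%, as stated. Section 5.3 gives no formal sample size calculation, so there is no power figure to reproduce.

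**What each primary measure observes.**

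| Measure | Observed in | Informs | Does not inform |
|---|---|---|---|
| Recruitment | Eligible patients asked to join a single-arm study | Uptake of this protocol | Uptake when allocation is by chance |
| Retention | 28 patients, all on RAGT | Completion on RAGT, including losses from relapse, medication change and health risk (section 7.5) | Completion in a comparator arm |
| Adherence | The 16 scheduled RAGT sessions | Deliverability of the training | Adherence to any comparator |
| Adverse events, Likert scale, observation | RAGT sessions and RAGT participants | Safety and acceptability of RAGT | Acceptability of a comparator or of chance allocation |

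No row yields an observation on randomisation or on a comparator: 28 patients on RAGT, 0 in a comparator, 0 randomised.

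**How readily a criterion can be met.** Retention of 85% needs 0.85 × 28 = 23.8, so 24 completers (24/28 = 85.7%). With the 10% attrition expected in section 5.3, the binomial probability of at least 24 completers out of 28 is 0.86. A pass on (b) is thus the likely result under the protocol's own expectation, and it carries no information on a comparator arm.

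**What joining involves.** In Table 8 the training is 16 × 45 = 720 minutes, all within routine. The timed additions are 70–90 (baseline) + 5 (goal setting) + 70–90 (post-intervention) = 145–185 minutes. On the timings given, the added time lies in assessment and goal setting, not in the training.

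**Illustration of what is at stake.** The inputs w and d are assumed; the protocol gives neither.

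- Recruitment: if a share w of consenting patients would also accept randomisation, the randomised rate is 3 × w per month. For w = 0.3 this is 0.9; for w = 1.0 it is 3.0.
- Retention with 1:1 allocation, 90% retention on RAGT and comparator drop-out d: overall retention = (0.90 + 1 − d)/2. For d = 0.10 this is 90%, for d = 0.20 it is 85%, and for d = 0.40 it is 75%. The 85% target is missed once d exceeds 20%.

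The study measures neither w nor d, so it cannot say where in these ranges a later trial would fall.

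**The case against.** A single-arm study is a legitimate first step before a randomised trial. Section 4.1 gives a reason for having no control, and the limitations list admits there is none. The objective is to explore, no go/no-go rule is attached to the criteria, and the stated uses are designing a later trial, refining procedures and informing hypotheses. Much of the primary endpoint (consent, completion, attendance, adverse events, acceptability, observation) does bear on feasibility of the methods. All of this stands. It does not remove the mismatch: the endpoint still names feasibility of the randomised trial, section 4.8 still ties success criteria to a larger trial, and the limitation is not connected to the primary objective.

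A reader might infer more than the documents support:

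- *That patients would receive the same RAGT whether or not they joined, so that refusing costs nothing.* Sections 7.1, 7.2 and 7.7 place the training in routine care, but none says that decliners get the same LEXO schedule. Section 1.1 says the plan specifies the sessions and that the site also uses another gait robot. Section 12.3 bars study interventions before consent.
- *That consent adds only tests and retention reflects only willingness to finish them.* Joining also requires availability for the full period and permission for outside treatment, and section 7.5 counts clinical exits as drop-outs. Such exits would plausibly occur in a randomised trial too.
- *That the later trial would withhold the robot, and that this is the step most likely to fail.* The comparator is never described, and nothing ranks the risks.
- *That the study cannot address its primary objective at all.* The part on the methods is addressed.

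**Conclusion.** The point holds in a limited form. The primary objective and endpoint, as worded, extend to feasibility of a full-scale randomised trial. The design supports a narrower statement: feasibility of recruiting to, delivering and assessing the RAGT protocol. Criteria (a) to (c) can all be met with no observation on acceptance of random allocation or on comparator-arm retention.

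This rests only on the stated design: one arm, no randomisation, no comparator. It does not depend on what decliners receive or on which comparator is later chosen. The documents do not allow the size of any over-optimism to be estimated; the figures of 0.9 to 3.0 patients per month and 75% to 90% retention show only how wide the unknown is under assumed inputs. It is a defect of wording and interpretation that should be corrected. It is not a reason to change the design, and no later analysis could supply the missing observations.

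**What to change.** 1. In section 2.2, section 4.8 and the synopsis, restate the primary endpoint as feasibility of the methods and of delivering and assessing the LEXO RAGT protocol, to inform the design of a later randomised trial.
2. State there and in the limitations list that criteria (a) to (c) do not establish acceptance of randomisation or retention in a comparator arm.
3. Optional: ask consenting participants one yes/no question on whether they would accept allocation by chance between RAGT and whichever comparator is planned. Include decliners only if the ethics committee agrees, since this means recording answers from people who have not consented. Report the proportion descriptively as hypothetical willingness, not as the recruitment estimate for the later trial.

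**Cost.** Items 1 and 2 change text only: no added visits, staff or patients, but a narrower stated conclusion, and the change must be documented and reported to the ethics committee under sections 6.3 and 12.2. Item 3 needs a small amendment and an explanation of chance allocation to patients in a study that has none, and the answers may overstate real acceptance.
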